**Methods:**

ARISE is a national, multicenter, non-inferiority randomized clinical trial. Two hundred patients with non-ST-segment elevation acute coronary syndrome will be randomized to either radial or femoral access using a vascular closure device. The primary outcome is the occurrence of vascular complications at an arterial puncture site 30 days after the procedure, including major bleeding, retroperitoneal hematoma, compartment syndrome, hematoma ≥ 5 cm, pseudoaneurysm, arterio-venous fistula, infection, limb ischemia, arterial occlusion, adjacent nerve injury or the need for vascular surgical repair.

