#### Statistical analysis

The primary analysis of the study is a non-inferiority comparison between the radial approach and femoral approach using VCD to decrease vascular complications at the arterial puncture site, in all randomized patients, based on the intention-to-treat principle.

Estimating a vascular complication rate pre-specified in the primary outcome of approximately 3% for the radial technique [19,32] and 12% for the femoral technique [26-31] and determining a non-inferiority margin of 0.15 based on historical data [18,19] with an alpha level of 0.05 and a beta level of 0.10, the minimum estimated sample size per group was established as 97 individuals. Twenty additional patients may be added to the final population to correct any subsequent loss of follow-up. This non-inferiority margin was derived from a trial that demonstrate the benefit of radial approach on the reduction of major vascular complications (hazard ratio, 0.37; 95% confidence interval, 0.27 to 0.52) as compared with femoral approach [18]. The non-inferiority margin of 0.15 was chosen in order to avoid a loss of greater than half the lower bound of the 95% confidence interval (0.27). The non-inferiority of the femoral approach with VCD will be declared if the lower confidence interval limit of 95% of the difference of both techniques does not include the specified inferiority margin value.

Categorical data will be presented as frequencies and group percentage and will be compared by chi-squared or Fisher’s exact tests. Continuous variables will be expressed as means and standard deviation and will be compared by Student’s *t-*test. Statistical analyses will be performed using Statistical Package for the Social Sciences for Windows (version 16.0; SPSS, Chicago, IL, USA).

The study was approved by the Dante Pazzanese Institute of Cardiology ethical committee, predicting and validating the Santa Casa de Marília as a co-participating institution. No extramural funding will be used to support this work. The authors are solely responsible for the design and conduct of this study, all study analyses and drafting and editing of the paper.

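### The stated 97 per group does not give 90% power at the plan's own rates (3% against 12%) and margin of 0.15; under the 95% confidence interval rule, power is about 30% to 40%

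*Protocol article*

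**What the plan says.** All the inputs and the result stand in one sentence of the protocol article, under Statistical analysis:

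- Rates: "Estimating a vascular complication rate pre-specified in the primary outcome of approximately 3% for the radial technique" and "12% for the femoral technique".
- Margin: "determining a non-inferiority margin of 0.15 based on historical data".
- Error rates and result: "with an alpha level of 0.05 and a beta level of 0.10, the minimum estimated sample size per group was established as 97 individuals".

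The same paragraph judges non-inferiority by a 95% confidence limit for the difference between the techniques. The margin of 0.15 therefore works as an absolute risk difference. The paragraph does not say whether alpha is one-sided or two-sided.

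On numbers, the section adds "Twenty additional patients may be added to the final population", and the abstract says "Two hundred patients with non-ST-segment elevation acute coronary syndrome will be randomized". The abstract and the study status section report 91 patients included by October 2013, with inclusion expected to run into the second half of 2014.

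**The concern.** In a non-inferiority trial, the sample size is driven by the distance between the expected difference and the margin. The stated rates put femoral access 9 points worse than radial against a margin of 15 points, so only 6 points remain. Ninety-seven per group is small for a distance of that size.

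The power claim for the primary comparison is at stake. Readers are told that the risk of missing non-inferiority is 10%. If the stated rates are true, that risk is several times larger. A trial that did not show non-inferiority could then be read as evidence against the closure device when low power would be a sufficient explanation.

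**Working it through.** **Inputs** (all from Statistical analysis): radial rate p1 = 0.03; femoral rate p2 = 0.12; margin M = 0.15 on the difference; beta = 0.10; alpha = 0.05 with sidedness not given. I tried both one-sided 0.05 and one-sided 0.025; the second is what a two-sided 95% interval implies. One size per group is quoted, so I assume 1:1 allocation.

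**Can 97 be reproduced?** The standard unpooled formula is

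n = (z_alpha + z_beta)² × [p1(1 − p1) + p2(1 − p2)] / [M − (p2 − p1)]²

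- Variance term: 0.03 × 0.97 + 0.12 × 0.88 = 0.0291 + 0.1056 = 0.1347.
- Distance: 0.15 − (0.12 − 0.03) = 0.06; squared, 0.0036.
- One-sided 0.05: (1.645 + 1.282)² = 8.564; 8.564 × 0.1347 / 0.0036 = 320.4, so **321 per group**.
- One-sided 0.025: (1.960 + 1.282)² = 10.507; 10.507 × 0.1347 / 0.0036 = 393.2, so **394 per group**.

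It cannot. The stated 97 is smaller by a factor of 3.3 (321/97) to 4.1 (394/97). Other variance choices ask for more: 331 or 405 with a pooled variance, and 359 or 445 with the Farrington-Manning method.

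**Power at 97 per group, 3% against 12%.** The standard error is √(0.1347/97) = 0.0373, and 0.06/0.0373 = 1.61. Power is Φ(1.61 − 1.960) = 36.3% at one-sided 0.025 and Φ(1.61 − 1.645) = 48.6% at one-sided 0.05. By method:

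| Method | One-sided 0.025 (two-sided 95% CI) | One-sided 0.05 |
|---|---|---|
| Normal, unpooled | 36.3% | 48.6% |
| Exact binomial, Wald limit | 39.9% | 48.9% |
| Exact binomial, Newcombe limit | 30.4% | 44.6% |

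The Farrington-Manning approximation is a little lower still, at 29.0% and 41.9%. By the unpooled approximation, 100 per group gives 37.3% and 49.6%, and 107 per group (all 20 optional patients used) gives 39.4% and 51.8%.

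**Other readings of the inputs** (per group; one-sided 0.05 / one-sided 0.025 unless noted):

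- 80% power instead of 90%: 232 / 294.
- Sign of the difference reversed (distance 0.24): 21 / 25.
- Both arms at 3%: 23 / 28.
- Superiority test of 3% against 12%, 90% power: 145 one-sided, 178 two-sided.

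**Calculations that land near 97:**

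- Both arms at 12%, one-sided 0.025: 10.507 × 2 × 0.1056 / 0.0225 = 98.6, so 99. Power at 97 is 89.5%.
- Both arms at 15%, one-sided 0.05: 8.564 × 2 × 0.1275 / 0.0225 = 97.06, so 98.
- 3% against 7.6%, one-sided 0.025: the variance term is 0.0291 + 0.0702 = 0.0993 and the distance is 0.104; 10.507 × 0.0993 / 0.0108 = 96.5, so 97.
- One-sided superiority test of 3% against 15%, alpha 0.05: 96.

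Each of these drops or replaces at least one stated input.

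**The case against.** The best defence is that 12% need not be the expected rate in the randomised femoral arm. The sentence names the femoral technique without the device, and the Background hypothesises that the device lowers complications. On that view, 12% is a historical femoral rate and the expected difference is smaller. The wording is ambiguous enough that the power figures must be stated as conditional on 3% and 12% being the true rates. But the defence does not rescue 97. If the device arm were expected to match radial at 3%, 23 or 28 per group would do. Several of the references cited for the 12% are also the closure-device meta-analyses and registries described under Percutaneous vascular closure devices.

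Three stronger readings are tempting, and the document does not support them.

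- A reader might infer that 97 can come only from assuming no true difference. It cannot be pinned down that way: 3% against 7.6% also gives 97, and the authors' method is not shown.
- A reader might infer that the totals contradict each other. They do not. The minimum is 2 × 97 = 194, the optional 20 raise it to 214, and the 200 in the abstract lies between the two.
- A reader might infer that the design could not have succeeded. Power of 30% to 49% is poor, but it is not zero, and power is about 90% under other plausible rates.

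**Conclusion.** The sample-size statement is wrong as written. If 3% and 12% are the true rates of the two arms and 0.15 is an absolute difference, 90% power needs about 321 per group (one-sided 0.05) or 394 (one-sided 0.025). At 97 per group, power is about 30% to 40% under a two-sided 95% interval, or about 45% to 49% at one-sided 0.05. Neither the unstated sidedness of alpha nor the choice of method changes the conclusion.

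Under the two-sided 95% interval, failure to show non-inferiority is more likely than success at these rates. That statement should not be stretched to every case: with 107 per group and one-sided 0.05, power is 51.8%. Equal rates of about 12% remain a possible explanation of the 97, not an established one.

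**What to change.** Keep the published 3% and 12% visible, because enrolment is under way and planning assumptions should not be silently replaced. Add a dated correction to the sample-size paragraph that:

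1. states which true rates in the two arms were actually used to obtain 97;
2. states the one-sided alpha that matches the confidence interval rule (0.025 if the 95% interval is two-sided);
3. restates power at the planned 97 to 100 per group for 3% against 12% (about 36% to 37% by the unpooled normal approximation at one-sided 0.025), and gives example scenarios in which power is about 90%, such as both arms near 12%, or 3% against about 7.6%.

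The cost is wording only. No extra patients are required, but the stated power becomes less favourable.

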### Strategies to prevent bleeding and vascular complications

#### Radial technique

Among the strategies to decrease vascular complications after invasive coronary procedures, the radial approach is an established one [15,16]. Although it has been adopted by only a few centers, it provides more comfort to patients, allows early ambulation, decreases hospital stay and shows less vascular puncture site complications [17]. In a comparative randomized trial between radial and femoral techniques involving 7,021 ACS patients submitted to invasive techniques, both techniques were shown to be safe and effective for PCI, with similar incidences of death, AMI, stroke and major bleeding at 30 days (3.7% versus 4.0%; *P* = 0.50) [18]. However, the radial approach displayed significantly decreased vascular complications, including pseudoaneurysm, large hematomas, arterio-venous fistula and limb ischemia requiring surgical intervention (1.4% versus 3.7%; *P* < 0.0001).

Given the small number of training centers that use the radial technique, the uncertainties concerning the learning curve which would be associated with a higher failure rate and more radiological exposure, and the lack of large-scale multicenter studies that can reproduce the excellent results obtained by highly experienced centers, the femoral approach remains the most popular for invasive coronary procedures [19].

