#### Outcomes

##### Primary outcome

Vascular complications at the arterial puncture site 30 days after the procedure (vascular complications at the arterial puncture site include major bleeding, retroperitoneal hematoma, compartment syndrome, hematoma ≥ 5 cm, pseudoaneurysm, arterio-venous fistula, infection, limb ischemia, arterial occlusion including asymptomatic occlusion, adjacent nerve injury or the need for vascular surgical repair).

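### The 0.15 margin is justified by a radial benefit on major vascular complications but applied to a broader 11-component composite with no historical effect shown, so the claim to keep half the benefit is unsupported

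*Protocol article*

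**What the plan says.** All places are in the protocol article.

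- **Statistical analysis, source of the margin.** "This non-inferiority margin was derived from a trial that demonstrate the benefit of radial approach on the reduction of major vascular complications". The effect cited is for "major vascular complications (hazard ratio, 0.37; 95% confidence interval, 0.27 to 0.52) as compared with femoral approach [18" (the bracketed number is the reference). The margin was "chosen in order to avoid a loss of greater than half the lower bound of the 95% confidence interval (0.27").
- **Statistical analysis, historical basis.** The plan speaks of "determining a non-inferiority margin of 0.15 based on historical data [18,19] with an alpha level of 0.05 and a beta level of 0.10". Two references are named, but only the first has a derivation written out.
- **Radial technique (Background).** In the same reference trial of 7,021 patients, radial access showed "significantly decreased vascular complications, including pseudoaneurysm, large hematomas, arterio-venous fistula and limb ischemia requiring surgical intervention (1.4% versus 3.7" per cent, radial first.
- **Primary outcome.** The ARISE composite has 11 components. Besides major bleeding, retroperitoneal hematoma, compartment syndrome, hematoma of 5 cm or more, pseudoaneurysm and arterio-venous fistula, it counts "infection, limb ischemia, arterial occlusion including asymptomatic occlusion, adjacent nerve injury or the need for vascular surgical repair".
- **Table 1.** Radial artery occlusion is the example given for asymptomatic arterial occlusion.
- **Statistical analysis, planning rates.** About 3% (radial) and 12% (femoral) are assumed for the primary outcome.

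**The concern.** A non-inferiority margin that claims to keep a share of the control's benefit needs an estimate of that benefit on the endpoint being tested. Here the estimate belongs to one endpoint and the test to another. The article neither gives a radial effect on the 11-component composite nor argues that the hazard ratio of 0.37 carries over to it.

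What is at stake is how a positive result would be read. The Conclusions section appeals to the proven efficacy of the radial approach. A reader told that femoral access with the device is non-inferior would take it that most of that benefit is kept. The composite can be non-inferior while the femoral excess on major vascular complications is fully present, if other components weigh against the radial arm.

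**Working it through.** **1. The plan's own figure.** Half of 0.27 is 0.27 / 2 = 0.135. The margin is 0.15, and 0.15 / 0.27 = 55.6%. The stated rule is thus met only roughly, and it treats a hazard-ratio limit as a difference in proportions. That is a separate fault. What matters here is that the input, 0.27, comes entirely from the source endpoint.

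**2. Do the hazard ratio and the Background rates describe the same endpoint?** 1.4 / 3.7 = 0.378, which agrees with the cited 0.37. The Background description can therefore be read as the endpoint behind the margin. Its absolute effect is 3.7 − 1.4 = 2.3 points.

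**3. The two endpoints side by side.**

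| Source endpoint, as described in Radial technique | ARISE Primary outcome |
|---|---|
| Pseudoaneurysm | Pseudoaneurysm |
| Large hematomas | Hematoma of 5 cm or more |
| Arterio-venous fistula | Arterio-venous fistula |
| Limb ischemia requiring surgery | Limb ischemia, with or without surgery |
| not named | Major bleeding |
| not named | Retroperitoneal hematoma |
| not named | Compartment syndrome |
| not named | Infection |
| not named | Arterial occlusion, including asymptomatic |
| not named | Adjacent nerve injury |
| not named | Vascular surgical repair |

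Four components are named for the source. ARISE has 11: seven more, and limb ischemia widened.

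**4. Which added components matter?** The rule uses the absolute difference, femoral minus radial. Treat events as additive, let the source rates hold, and let the added components contribute *f* points in the femoral arm and *r* in the radial arm:

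difference on composite = (3.7 + *f*) − (1.4 + *r*) = 2.3 + *f* − *r*

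- If *f* = *r*, the difference stays at 2.3. Components equal in both arms mask nothing. They only add variance.
- If *r* exceeds *f*, the composite difference shrinks while the source-endpoint excess of 2.3 points is untouched.

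The documents give no rate for asymptomatic radial occlusion, so *r* is an assumption. With *f* = 0:

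| *r* (points) | Femoral | Radial | Difference |
|---|---|---|---|
| 0 | 3.7% | 1.4% | +2.3 |
| 1 | 3.7% | 2.4% | +1.3 |
| 2.3 | 3.7% | 3.7% | 0 |
| 3 | 3.7% | 4.4% | −0.7 |

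At *r* = 3 the sign reverses, although nothing has changed on major vascular complications.

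**5. What ARISE could say on the source endpoint.** With 97 per group and the source rates, expected events are 97 × 0.037 = 3.6 and 97 × 0.014 = 1.4, about 5 in all. The 95% half-width is 1.96 × √(0.037 × 0.963 / 97 + 0.014 × 0.986 / 97) = 0.044, or 4.4 points. The contrast can be described but not tested with any force.

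**The case against.** **The source definition is not fully known.** The Background list opens with the word "including", and the second reference cited for the margin is not shown. This stands: four is the number of components named, not a proven total. But no effect on the ARISE composite is stated from either source, and the only derivation written out uses the first.

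**Dilution makes passing harder, not easier.** A reader might infer that any component without a radial advantage dilutes the contrast and eases a pass. On the absolute scale this is wrong. Adding 5 points to both arms lowers the probability of meeting the 0.15 rule from 98.8% to 87.6% (exact enumeration, Newcombe interval, 97 per group, starting from 3.7% and 1.4%). Only components leaning to the radial arm can mask a femoral excess.

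**The high pass probability is not the cost of the mismatch.** Under the source rates, the rule is met 98.8% (Newcombe) to 99.6% (Wald) of the time. That reflects 15 points set against 2.3, a ratio of 6.5. It would be the same if ARISE used exactly the source endpoint, so it belongs to the separate question of the margin's size.

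**The bleeding result is weak evidence.** The source trial's "similar incidences of death, AMI, stroke and major bleeding at 30 days (3.7% versus 4.0" per cent might suggest no radial advantage on bleeding. It pools four outcomes, whereas ARISE counts major bleeding at the puncture site and lists unrelated major bleeding separately. It says little about access-site bleeding either way.

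**The direction of the net effect is unknown.** The planning rates give 12 − 3 = 9 points on the composite, more than the source's 2.3. If they were right, the added components would lean against the femoral arm. This stands as a limit on the illustration. But 3% and 12% are assumptions, and the plan does not derive its margin from them.

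**Conclusion.** The point holds as a mismatch between the endpoint that justifies the margin and the endpoint it is applied to. The stated property, that no more than half of the radial effect can be lost, is not shown for the ARISE composite. Any margin recalculated from the same trial would inherit the problem.

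The size of the harm cannot be fixed from the documents. In the illustration, a radial-arm excess of 2.3 points on the added components hides the whole source effect, and 3 points reverses the sign. This rests on three assumptions: the Background list adequately describes the source endpoint, its rates carry over to ARISE, and events are additive. The rate of asymptomatic radial occlusion is also assumed.

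The documents do not support the stronger readings that the added components generally make the composite easier to pass, or that the mismatch itself produces a near-certain pass. The change is worth making because it alters what the trial may conclude. It does not repair the scale or size of the 0.15 margin.

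**What to change.** In Statistical analysis:

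1. Withdraw the statement that the margin preserves half of the source trial's effect. Say that the source trial measured a narrower endpoint, and that non-inferiority on the ARISE composite does not by itself show that the radial benefit on major vascular complications is retained.
2. Pre-specify a supplementary intention-to-treat composite as close to the source list as the collected components allow: pseudoaneurysm, hematoma of 5 cm or more, arterio-venous fistula, and limb ischemia with surgical repair. The mapping is an assumption and should be labelled so, since 5 cm stands in for large hematomas and the last item combines two ARISE components. Report the femoral-minus-radial difference with its 95% CI beside the primary result, descriptively.

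Do not add a pass/fail threshold at 2.3 points. With 97 per group and a true rate of 1.4% in both arms, it would be met only 11.8% (Newcombe) to 31.2% (Wald) of the time. With no events in either arm, the Newcombe upper limit is still 3.8 points.

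Cost: wording and one table. Individual components are already secondary outcomes, so no patients or procedures are added. Enrollment stood at 91 of 200 at the article's status report, so pre-specification was still possible then. The downside is a more modest claim and a wide supplementary interval.

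### The 0.15 non-inferiority margin does not follow from its stated derivation: it exceeds half of 0.27, treats a hazard ratio as a risk difference, and starts from the optimistic confidence bound

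*Protocol article*

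**What the plan says.** All of the derivation is in the Statistical analysis section of the protocol article.

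- Planning rates for the primary outcome are "approximately 3% for the radial technique [19,32"] and "12% for the femoral technique [26-31"].
- The margin is introduced as "determining a non-inferiority margin of 0.15 based on historical data [18,19"].
- Its source is a trial of radial against femoral access, with "hazard ratio, 0.37; 95% confidence interval, 0.27 to 0.52".
- The rule linking source to margin is that 0.15 was "chosen in order to avoid a loss of greater than half the lower bound of the 95% confidence interval (0.27").
- The decision rule works on a difference: non-inferiority of femoral access with the closure device is declared "if the lower confidence interval limit of 95% of the difference of both techniques does not include the specified inferiority margin value".

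The Background, under Radial technique, gives the same trial's vascular complication rates as "1.4% versus 3.7" per cent.

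**The concern.** The margin is the decision threshold of the primary analysis. The article presents it as capping the loss at half of an effect shown in a cited trial, so a reader would take a positive result to mean that much of the radial advantage is kept.

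Each link in that argument breaks. The number does not satisfy the rule given for it. The rule halves a ratio and uses the result as an absolute difference. The bound that is halved is the one at which radial access looks best. If the margin is wider than the whole radial advantage, femoral access could be shown to be worse and still be declared non-inferior on a justification that says the opposite.

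**Working it through.** **Inputs.** Margin 0.15; hazard ratio 0.37 with limits 0.27 and 0.52; planning rates 3% and 12%; alpha 0.05 (sidedness not stated), beta 0.10; 97 per group (all Statistical analysis). Total of 200 patients, so 100 per arm (Abstract, Methods). Cited trial's rates 1.4% and 3.7% (Background, Radial technique).

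**1. On which scale does 0.15 act?** The decision rule refers to a difference, and the sample size agrees. With the unpooled normal approximation, n per arm = (z₁₋α + z₁₋β)² × [p₁(1−p₁) + p₂(1−p₂)] / (margin − true difference)².
- 12% in both arms, one-sided 0.025, 90% power: 10.507 × 0.2112 / 0.15² = 98.6, so 99. This is within 2 of the stated 97.
- 3% versus 12% as stated: 10.507 × 0.1347 / 0.06² = 393.2, so 394 (321 at one-sided 0.05).

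So 97 is approached from a stated rate only with 0.15 as an absolute risk difference and no true difference between arms.

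**2. The half rule.** 0.27 / 2 = 0.135. The margin is 0.15 / 0.27 = 56% of the bound. Rounding does not explain the gap, and it goes in the looser direction.

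**3. Scale.** 0.27 is a hazard ratio. Half of it is not a number of percentage points, and no base rate is used to convert it.

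**4. Bound.** For radial against femoral, 0.27 is a 73% reduction and 0.52 a 48% reduction. The benefit the cited trial supports at its confidence level is the smaller one.

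**5. Size against the benefit.**
- Plan's own rates: 12% − 3% = 9 points; 15 / 9 = 1.7.
- Even the optimistic bound applied to 12%, with the hazard ratio treated as a risk ratio: 12 × 0.73 = 8.8 points in total, 4.4 when halved.
- Cited trial: 3.7% − 1.4% = 2.3 points in total, on a narrower endpoint.

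**6. What could pass.** Take 100 per arm, 3% radial and 10% femoral. SE = √[(0.03×0.97 + 0.10×0.90)/100] = 0.0345. The femoral-minus-radial difference is 7 points, Wald 95% CI 7 ± 1.96 × 3.45 = 0.2 to 13.8. The interval excludes zero and lies below 15. An uncorrected chi-squared test agrees (p = 0.045); Fisher's exact test gives p = 0.08, so the example sits at the edge of significance.

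**7. Reference margin from 0.52** (assumption: hazard ratio ≈ risk ratio). 1/0.52 = 1.92; half retention on the log scale gives √1.92 = 1.39.

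| Base rate | Log-scale half | Linear half |
|---|---|---|
| 3% radial | 3 × 0.387 = 1.2 points | (3/0.52 − 3)/2 = 1.4 points |
| 12% femoral (radial 12 × 0.52 = 6.24%) | 6.24 × 0.387 = 2.4 points | 12 × 0.48/2 = 2.9 points |

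Power against 1.16 points with 97 per arm and 3% in both: SE = √(2×0.03×0.97/97) = 0.0245; Φ(0.0116/0.0245 − 1.96) ≈ 7%.

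**8. Power at 0.135 beside 0.15, 97 per arm.**

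| Rates and criterion | Margin 0.15 | Margin 0.135 |
|---|---|---|
| 3% vs 12%, one-sided 0.05 | 49% | 33% |
| 3% vs 12%, 95% CI | 36% | 23% |
| 12% in both, 95% CI | 89.5% | 82.5% |

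**The case against.** The three errors have no good defence. The derivation is affirmatively stated, so condensation into an article does not explain it, and no unseen analysis plan can make 0.15 at most half of 0.27. The article also cites a second source [19] for the margin, whose content is not shown, but the derivation sentence rests only on [18].

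The stronger objections concern how far the point reaches. Four readings are tempting and go too far.

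- *Obeying the rule would drop power from 90% to 33% or 23%.* Not so. At 3% versus 12%, power with 0.15 is already 49% or 36%. The halving slip costs 16 or 14 points (7 points with 12% in both arms); the rest is a separate sample-size problem.
- *The margin is 6.5 times the radial benefit (15/2.3), or 13 times half of it.* Those multiples use the cited trial's endpoint: pseudoaneurysm, large hematoma, fistula and limb ischemia needing surgery. This trial's composite adds, among others, major bleeding, infection, nerve injury and asymptomatic occlusion. The comparison on the plan's own rates is 1.7 times.
- *A correct margin could be as large as 5 points.* From the 0.52 bound with log-scale retention, 5 points needs a radial rate of about 5/0.387 = 12.9%, which the article nowhere assumes. Half of the planned 9-point gap is 4.5 points, but that does not use the 0.52 bound.
- *Any positive result would be invalid.* A conclusion that the excess is below 15 points would stand as such. What lacks support is reading it as keeping the radial benefit.

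**Conclusion.** The stated basis for the primary decision threshold is wrong in arithmetic, in scale and in choice of bound. These three findings depend on no assumption about event rates. Replacing 0.15 by 0.135 would mend only the first, and halving 0.52 directly would repeat the scale error.

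On the plan's own rates the margin is 1.7 times the whole radial advantage and preserves none of it. This takes 3% and 12% as the radial and femoral rates, as the article labels them. The 1-to-3-point reference range also assumes that the hazard ratio approximates a risk ratio and that the cited effect carries over to a broader composite; neither can be checked from the article. The documents do not support inferring that the trial must be resized on this point alone, or that one particular replacement margin is the only correct one.

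**What to change.** Make these changes without looking at data by arm.

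1. Delete the statement that 0.15 limits the loss to half of the cited effect.
2. If 0.15 is kept because the trial is already enrolling, describe it as a pragmatic margin that the cited trial does not support. Limit the permitted conclusion to an excess below 15 percentage points, and do not claim that the radial benefit is preserved.
3. State a reference margin derived on one scale from the 0.52 bound: a ratio of about 1.39, or roughly 1 to 3 points (1.2 to 1.4 from a 3% radial rate, 2.4 to 2.9 from a 12% femoral rate). State the base rate, the retention scale and the risk-ratio assumption.
4. Report the same 95% CI beside that reference as context for interpretation and not as a second test. Power against it is very low (about 7% in the case worked above), so failing to exclude it would say little.
5. If power at 0.135 is quoted, give the figure at 0.15 next to it.

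The cost is wording and one extra line in the results. The real price is that the justification reads less favourably and the claim available after a positive result is narrower.

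### The non-inferiority rule names the lower limit of a difference with no direction and a margin with no minus sign, so it is valid only under a convention the protocol does not state

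*Protocol article*

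**What the plan says.** All of this is in the Statistical analysis section of the protocol article, except the outcome definition.

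- The primary analysis is "a non-inferiority comparison between the radial approach and femoral approach using VCD", by intention to treat.
- The outcome, under Primary outcome, is "Vascular complications at the arterial puncture site 30 days after the procedure". It is a harm, so a higher proportion is worse.
- The planning rates are "approximately 3% for the radial technique" and "12% for the femoral technique", "with an alpha level of 0.05 and a beta level of 0.10" and a minimum of 97 per group.
- The margin is introduced by "determining a non-inferiority margin of 0.15 based on historical data" and is printed once more in the same paragraph, again as 0.15 with no minus sign.
- The success criterion is that non-inferiority of the femoral approach with the device is declared "if the lower confidence interval limit of 95% of the difference of both techniques does not include the specified inferiority margin value".

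Nowhere does the article define the subtraction, give the margin a negative sign, or say that the limit must lie above or below it.

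**The concern.** For a harm outcome there are two equivalent correct rules. Either the upper limit of femoral minus radial lies below +0.15, or the lower limit of radial minus femoral lies above -0.15. The article's sentence takes the lower limit from the second rule and the positive margin from the first.

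The verb adds a further ambiguity. A limit is one number and cannot include another. If the interval is what was meant, an interval lying entirely above +0.15 also fails to include it. That interval would show femoral access to be worse by more than the margin, yet it would satisfy the wording.

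This sentence alone decides the trial's primary conclusion. An analyst who follows the text has to choose among readings that can give opposite answers on the same data.

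**Working it through.** **Inputs.** From Statistical analysis: radial rate 3%, femoral rate 12%, margin 0.15, a 95% interval and n = 97 per group. The other femoral rates (18%, 23%, 25%, 28%, 33%) are assumptions of this check. The first of them is 0.03 + 0.15 = 0.18, a true difference exactly on the margin.

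**The plan's own figure.** The value 97 is used only as the arm size. The usual formula is n = (1.960 + 1.282)² × [p1(1 - p1) + p2(1 - p2)] / (margin - true difference)².

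- With 12% in both arms it gives 10.51 × 0.2112 / 0.0225 = 98.6, close to 97.
- With 3% and 12% it gives 10.51 × 0.1347 / 0.06² = about 394.

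That gap is a separate matter and does not affect the reading of the decision rule.

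**Method.** Let d = x_F/97 - x_R/97, with Wald limits d ± 1.96 × √[p_R(1 - p_R)/97 + p_F(1 - p_F)/97] at the observed proportions. For each pair of true rates, sum the binomial probabilities of all 98 × 98 outcomes that satisfy the rule.

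**Readings.**

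- A: femoral minus radial, lower limit below +0.15.
- B: the interval for femoral minus radial excludes +0.15 on either side.
- C: radial minus femoral, lower limit above -0.15. This is identical to the upper limit of femoral minus radial being below +0.15, and it is the valid rule.

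**Probability of declaring non-inferiority, 97 per arm, Wald interval:**

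| True radial vs femoral | A | B | C (valid) |
|---|---|---|---|
| 3% vs 12% (planning rates) | 99.99% | 39.9% | 39.9% |
| 3% vs 18% (on the margin) | 98.2% | 5.5% | 3.7% |
| 3% vs 23% | 82.6% | 17.6% | 0.2% |
| 3% vs 25% | 69.7% | 30.4% | 0.05% |
| 3% vs 28% | 46.5% | 53.5% | 0.01% |
| 3% vs 33% | 15.0% | 85.0% | under 0.01% |

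With the Newcombe interval, column C is 30.4% at 3% vs 12% and 2.4% at 3% vs 18%. Column A hardly changes (98.2% at 3% vs 18%).

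A fourth reading takes radial minus femoral but keeps +0.15 as printed, with the lower limit required to be below it. That passes essentially 100% of the time in every row.

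**What drives the errors.**

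- Under A at 3% vs 18%, the lower limit lies above 0 and below 0.15 in 94% of trials. Femoral access would be significantly worse and still be declared non-inferior.
- Under B at 3% vs 25%, almost all of the 30.4% comes from intervals wholly above 0.15.

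**Worked example.** Take 3/97 radial events and 22/97 femoral events. Then d = 19/97 = 0.196, the standard error is 0.046, and the 95% limits are 0.106 and 0.286. A declares non-inferiority, because 0.106 is below 0.15, although the estimate itself exceeds the margin. C does not, because 0.286 is above 0.15. B does not, because 0.15 is inside the interval.

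**The case against.** The strongest defence is that the intended rule can be recovered. The article consistently names radial first and femoral second. Subtracting in that order makes the lower limit the right one for a harm outcome, and margins are often quoted as magnitudes. On that reading the rule is sound and rejects as it should (3.7% at the margin). This stands as an account of what was probably meant. It does not repair the text, because neither the order of subtraction nor the negative sign is stated, and both are needed.

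It could also be said that an article may leave detail to an analysis plan that is not shown. That holds for the type of interval: the choice between Wald and a score method is such detail. It does not hold for the success criterion, which the article states and states defectively.

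A reader might infer three stronger points that the document does not support:

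- That the rule passes almost always, even when femoral access is clearly inferior. No single reading in the table shows both. Reading A never passes an interval wholly above 0.15, and it falls to 46% at 3% vs 28% and 15% at 3% vs 33%. Reading B passes such intervals but is not near-automatic. The fourth reading is near-automatic, but it requires ignoring that a lower bound on radial minus femoral calls for a negative margin.
- That the primary outcome will be decided by a test of equality, because categorical data "will be compared by chi-squared or Fisher’s exact tests". That sentence is general text on data presentation in a separate paragraph, and nothing ties it to the primary decision.
- That the alpha level conflicts with the interval. An alpha of 0.05 is the two-sided complement of a 95% interval, so only the word two-sided is missing.

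**Conclusion.** The point holds as a defect of the written rule. It is not evidence that the sponsor intends an invalid analysis. As printed, the criterion is valid only if the reader adds two unstated elements, radial minus femoral and a margin of -0.15.

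The choice of reading matters under the plan's own assumptions. At 3% versus 12%, the probability of declaring non-inferiority is 99.99% under A and 40% (Wald) or 30% (Newcombe) under the valid rule. On the margin it is 98% against 3.7% or 2.4%.

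These figures assume 97 evaluable patients per arm, independent binomial outcomes and a 3% radial rate. With 100 per arm they change little (98.2% for A and 3.7% for the valid rule on the margin, Wald). The correction should be made because the sentence controls the primary conclusion.

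**What to change.** Replace the decision sentence with: non-inferiority of the femoral approach with the closure device is declared if the upper limit of the two-sided 95% confidence interval for the 30-day risk difference (femoral with device minus radial) is below +0.15; equivalently, if the lower limit for radial minus femoral is above -0.15. Add that this corresponds to a one-sided alpha of 0.025. Naming the interval method, for example a score-based one, is optional and can sit in the analysis plan.

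The cost is one sentence, with no change to data collection. Study status reports 91 patients included by October 2013, with inclusion expected to continue into the second half of 2014. The wording should be fixed, and dated, before anyone compares outcomes by arm.
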